## Methods and analysis

### Study design

The study has been designed as a feasibility waiting-list randomised controlled trial (RCT) with an integrated process evaluation. Participants will be randomised to YES exposure (phase 1) or a waiting list control and followed up for 6 months. At the 6-month follow-up point, control participants will then be exposed to YES, in a phase 2 exposure. Both groups will be subsequently followed up for a further 6 months. This will ensure that all eligible young people will have the opportunity to participate in the programme while maintaining a controlled structure to YES exposure that will allow us to explore differences. Conducting an additional 6-month follow-up after phase 1 will also enable us to assess how sustainable the intervention is over a longer time period. The adoption of a waiting list design is important as it overcomes the ethical dilemma of denying control participants the opportunity to benefit from the programme. The study design is presented schematically in figure 1.

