### Participants and sample size

We aim to recruit 50 young people and randomise half to the phase 1 programme exposure, and half to the phase 2 exposure. The inclusion criteria will involve:

Age 14–19 years.Diagnosis of T1DM.Suboptimal glycaemic control (HbA1c>69 mmol/mol or 8.5%).^3^No current or planned attendance of other structured education programmes.

Participants will be excluded if they: have a severe physical or mental illness, unstable retinopathy, significant learning difficulties; are unable to communicate in English; or are pregnant. Participants meeting the inclusion criteria will be recruited opportunistically at the participating centres through clinical referrals and patient database searches. Based on recruitment to the pilot study, we estimate that we will be able to recruit >30% of eligible patients. To increase engagement, we will run the full study, including programme occurrences and follow-up sessions, during school holidays as this was identified by young people as the optimal period for running the YES programme.

As a feasibility evaluation, the study is not statistically powered to estimate a clinical effect. Instead, we aim to estimate the effect-size/SD of outcomes to formulate a power calculation for a definitive trial. National Institute for Health Research guidance indicates that samples of 24–50 are adequate for this purpose.^33–35^ We have inflated our sample to allow for an estimated 20% drop-out rate.

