### Intervention and control conditions

The intervention is the YES programme as previously described. The programme exposure is sequenced as follows: (1) initial contact from the youth worker introducing the YES intervention; (2) recruitment to the study by researchers; (3) attendance at three all-day YES sessions in non-healthcare settings (groups of 10); (4) postprogramme networking through social media and (5) follow-up events facilitated by the youth worker. Sessions will be led by a peer-educator and a health professional and delivered face to face. Participants in the waiting-list control arm of the study will receive usual care following initial randomisation and will be exposed to the YES intervention at 6 months (phase 2 exposure). Usual care in this patient population typically involves outpatient consultations. To minimise potential external confounding factors, we will monitor any other educational interactions that participants might experience during the follow-up period in both groups.

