### Outcome measures

As a feasibility study, the objective is to optimise outcome selection and determine outcome effects prior to a definitive RCT. The primary outcome to assess the potential clinical effect of the programme will be HbA1c and we will examine: (1) the number of participants achieving clinically significant reductions of 5.5 mmol/mol or more and mean differences between groups over time, and (2) the SD of the mean difference between the intervention and control group in HbA1c at 6 months; for the control group, the SD of the mean difference between HbA1c at 12 months and preexposure (phase 2) and for the phase 1 intervention group, the SD of the mean HbA1c difference between post (6 and 12 months) and pre-exposure. While HbA1c is a proxy measure of complication risk, it is the most commonly adopted measure for determining the short to medium-term impact of an intervention and is the recommended measure from the National Institute for Health and Care Excellence for assessing the clinical and health economic benefits of diabetes interventions. In addition, our preliminary work and logic model show that the programme can mediate health behaviours by impacting on the psychosocial factors that can mediate self-management activation leading to improved glucose control. Hence, we will also assess the psychosocial and behavioural impacts of the programme, using the following secondary outcome measures:

Number of participants with 20% increase in frequency of blood glucose monitoring.Insulin adherence measured by self-report scale.Self-Management of Diabetes in Adolescence Scale.^36^Confidence in managing own healthcare (Confidence in Diabetes Self-Care Scale.^37^Diabetes Quality of Life Instrument-adapted for youth.^38^Illness perception (Brief Illness Perception Questionnaire).^39^Emergency care events (ambulance call-outs, accident and emergency attendance or hospitalisations).Hypoglycaemia (blood glucose<3.5 mmol/L) and severe hypoglycaemic events (requiring third party assistance).Weight.Intervention Appropriateness Measure.Feasibility of Intervention Measure.Acceptability of Intervention Measure.

For each outcome, we will assess differences in preexposure and postexposure, as well as differences between control and intervention groups.

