### Data analysis

The data will be analysed to determine the proportion of patients achieving the progression criteria; and the target reduction in HbA1c from baseline to follow-up (6 and 12 months), which will be estimated in both intervention (YES) and control groups. We will also estimate the SD of the mean difference between the intervention and control group in HbA1c at 6 months; for the control group, the SD of the mean difference between HbA1c at 12 months and pre-exposure (phase 2) and for the phase 1 intervention group, the SD of the mean HbA1c difference between post (6 and 12 months) and pre-exposure. These data will help inform the sample size calculation for a definitive trial.

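### Between-group effect estimates are not confined to the randomised first 6 months, and the phase 1 HbA1c pre/post change is uncontrolled after selection above 69 mmol/mol

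*Protocol article*

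**What the plan says.** *Outcome measures* closes its list with one rule for everything on it: "For each outcome, we will assess differences in preexposure and postexposure, as well as differences between control and intervention groups". The sentence gives no time point and does not say which of the two comparisons is the effect estimate.

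For HbA1c the text is more detailed but uneven:

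- The between-group SD has a fixed time: "the SD of the mean difference between the intervention and control group in HbA1c at 6 months".
- The between-group mean does not: "mean differences between groups over time".
- The control arm's post-YES change starts from the right place: "for the control group, the SD of the mean difference between HbA1c at 12 months and preexposure (phase 2").
- *Data analysis*, however, plans "the target reduction in HbA1c from baseline to follow-up (6 and 12 months), which will be estimated in both intervention (YES) and control groups", which runs the control group from baseline to 12 months.

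On exposure, *Study design* says "At the 6-month follow-up point, control participants will then be exposed to YES, in a phase 2 exposure", and *Intervention and control conditions* repeats that this arm "will be exposed to the YES intervention at 6 months (phase 2 exposure"). On entry, *Participants and sample size* requires "Suboptimal glycaemic control (HbA1c>69 mmol/mol or 8.5"%).

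The progression text after Figure 1 says that effects on the target behaviours and on glycaemic control will be used to judge the programme's potency and to decide on a definitive trial.

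**The concern.** Two quantities that the text allows do not isolate the programme.

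The first is any control-versus-intervention figure that reaches 12 months. By then both arms have had YES, so a between-arm difference compares early with delayed exposure. A control reduction from baseline to 12 months likewise mixes 6 months of usual care with 6 months after YES.

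The second is the phase 1 arm's own HbA1c change from baseline, with the responder count built on it. Participants enter because their HbA1c is high. Part of that excess is temporary, so the next value tends to be lower whatever is done.

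The study disclaims effect testing, but its estimates still inform the go/no-go decision and the next sample size. If the effect estimate is not named, the most favourable of several candidate figures could be taken as evidence of potency.

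**Working it through.** **Stated figures.** The plan gives no figure for either bias, so there is none to reproduce. Its sample size of 50 is consistent with 40 completers inflated for 20% drop-out: 40 / (1 − 0.20) = 50. The 40 is back-calculated, not stated.

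**Regression to the mean in HbA1c**

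Inputs from the article: 10% of those aged 14–19 at or below 48 mmol/mol and a fifth above 75 (*Introduction*); entry above 69; responder threshold a fall of 5.5. Assumptions: normality, the qualifying value serves as baseline, no time trend, and equal correlation r between visits. The documents give no r, so a range is shown.

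1. SD = (75 − 48) / (0.8416 + 1.2816) = 12.72. Mean = 48 + 1.2816 × 12.72 = 64.3.
2. Under this fit 36% exceed 69, and their mean is 77.6, an excess of 77.6 − 64.3 = 13.3.
3. Expected fall with no effect = (1 − r) × 13.3. The share with a fall of 5.5 or more comes from simulation.

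| Assumed r | Expected fall, no effect | Responders, no effect | Responders, true effect 5.5 |
|---|---|---|---|
| 0.6 | 5.3 | 49% | 69% |
| 0.7 | 4.0 | 43% | 66% |
| 0.8 | 2.7 | 36% | 63% |
| 0.9 | 1.3 | 23% | 59% |

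With a true effect of 5.5 mmol/mol, the uncontrolled responder share is 59% to 69%. The part due to the programme is the difference from the no-effect column: 69 − 49 = 20 points at r = 0.6 and 59 − 23 = 36 points at r = 0.9. Only the randomised 6-month comparison shows that difference; the phase 1 arm alone cannot.

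In the same simulation the 6-to-12-month drift is about 0, because the 6-month value was not selected on. The control arm's change from its own pre-exposure value is therefore largely free of this artefact.

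**The 12-month contrast**

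For illustration, give each arm a YES effect of 5.5 mmol/mol, and let the phase 1 arm retain a fraction f of it at 12 months.

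- 6 months, randomised: 5.5 − 0 = 5.5.
- 12 months: 5.5f − 5.5, which is 0 for f = 1, −2.75 for f = 0.5, and −5.5 (favouring controls) for f = 0.
- Control arm, baseline to 12 months, r = 0.6: an expected fall of 5.3 + 5.5 = 10.8, none of it usual care.

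**The case against.** The best defence is that the protocol already leans the right way. The abstract places outcome evaluation at 6 months, the between-group SD is fixed there, and *Study design* gives the further follow-up of phase 1 a sustainability role. The control SD is anchored at phase 2 pre-exposure, so the authors had seen the crossover. *Data analysis* can be read as within-arm estimation only. The numeric progression criteria are recruitment and completion.

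Much of this stands. A reader might infer that a 12-month control-versus-intervention test is planned, but no sentence specifies one. What remains is that the between-group mean carries no time limit and that the 12-month reduction is reported under the label of control.

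It is also tempting to say that every outcome is distorted by regression to the mean. Selection is on HbA1c alone, so other outcomes are touched only through their correlation with it. The randomised 6-month comparison is not affected in expectation.

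Nor can the pilot's 46% responder rate be explained this way: the article gives no HbA1c entry threshold for the pilot, and its follow-up was 12 months.

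The size is model-dependent, and at r = 0.9 it is small. The abstract links adolescence with worsening glycaemia, which could offset part of the fall. That makes the pre/post change harder to read in either direction, and a concurrent control deals with both influences.

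**Conclusion.** The point holds in limited form. The text does not confine between-group effect estimates to the randomised 0–6 month period, and the phase 1 HbA1c change and responder count are uncontrolled after selection above 69 mmol/mol.

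With no effect, the expected fall is about 1.3 to 5.3 mmol/mol, with 23% to 49% responders, for r from 0.9 to 0.6. The upper end is close to the protocol's own 5.5 threshold. These figures rest on the assumptions listed with the calculation; the direction does not depend on the exact r, provided it is below 1. A 12-month contrast would show nothing, or favour controls, when an effect equal in both arms is kept or wanes in phase 1.

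The rule for each outcome also takes in the Appropriateness, Feasibility and Acceptability measures, which rate a programme that unexposed people have not received. One might infer that the plan schedules them before exposure, but the process evaluation text does not. This is loose drafting with little analytic consequence.

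**What to change.** Revise *Outcome measures* and *Data analysis* to say:

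- The HbA1c effect estimate is the 6-month between-arm comparison among randomised participants, adjusted for baseline HbA1c, together with the between-arm difference in the proportion with a fall of 5.5 mmol/mol or more. Other outcomes with a baseline value use the same 6-month contrast.
- Pre/post changes and all 12-month results, including any early-versus-delayed summary, describe durability and are not evidence of effect or potency.
- The control arm's post-YES change is measured from its 6-month pre-exposure value throughout.
- The Appropriateness, Feasibility and Acceptability measures are reported after exposure only (a minor wording point).

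The cost is wording; visits, data collection and the sample of 50 are unchanged. Pre/post results lose weight, and the 6-month estimate will be imprecise. Under the fitted SD, with 50 × 0.8 = 40 completers (20 per arm, all randomised), the adjusted standard error is 12.72 × √(1 − r²) × √(2/20). This is 3.2 at r = 0.6 and 1.8 at r = 0.9, or 95% half-widths of about 6.3 and 3.4 mmol/mol (× 1.96). The potency judgement should be worded with that width in view.

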### Study procedure

Potential participants will be recruited from the participating diabetes centres. Since it can be challenging to engage young people with T1DM, especially those from deprived and ethnically diverse groups, a youth worker role will be incorporated into the recruitment process to identify potential participants and support them in considering participation in the study. Young people will then be screened for eligibility and consented. Parental consent will also be gained from those aged <16 years of age. We will ask eligible young people who decline participation to give a reason for their decision. The participants will then be randomly allocated as previously described.

### Data collection and storage

Data (questionnaires, body weight and medical-record data) will be collected at baseline, then again at 6 and 12 months. Baseline data will also include: sociodemographics; education/employment; and diabetes self-management behaviours including insulin use and blood glucose testing. Patient records will be examined to collect data on: HbA1c; hospitalisations and emergency care; diabetes education attendance; screening attendance; and attendance at appointments. For baseline, this will be all events in the preceding 12 months, and postexposure will be for the 12 months following exposure (or 6 months’ post exposure for those exposed at phase 2). Analysis will be on-treatment, as the primary aim of this study is to assess feasibility. Data will be coded and cleaned by statisticians and stored on an encrypted shared drive.

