To assess perception of how appropriate, acceptable and feasible the programme is to young people and healthcare professionals, we will use previously validated short pragmatic surveys.^45^ This will allow quantitative assessment against the study end-points. We will also undertake:

An audit of the number of eligible young people that decline participation, considering their clinical and sociodemographic profiles.An audit of intervention fidelity using an adherence checklist based on the YES protocol.Exit questionnaires with attending young people to rate programme satisfaction and utility; and to identify three strengths, weaknesses and areas for improvement.

The audit and questionnaire data will be analysed to examine the utilisation and satisfaction with the programme. Intervention fidelity will be assessed from the audit data detailing the delivery of the different intervention components. We will also monitor control conditions in the first 6 months to consider whether any extraneous interventions or clinical changes occurred that might impact on the observed outcomes. While the study will be recruiting participants from five diabetes centres, we do not anticipate significant site level effects on outcomes as the intervention will be delivered by the same clinicians and peer educators throughout, following the YES curriculum. However, we will monitor any variations in the general care for each centre, or any changes in the care provided to the target population during the follow-up period.

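### The record-based event windows leave out the waiting-list arm's months 0 to 6 and set 12 months against 6, so emergency-care and attendance comparisons need redefined windows

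*Protocol article*

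**What the plan says.** Data collection and storage gives the schedule: "Data (questionnaires, body weight and medical-record data) will be collected at baseline, then again at 6 and 12 months". It then lists what is taken from patient records, including hospitalisations and emergency care, screening attendance and appointment attendance, and fixes the periods covered. Before exposure: "For baseline, this will be all events in the preceding 12 months". After exposure: "postexposure will be for the 12 months following exposure (or 6 months’ post exposure for those exposed at phase 2".

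Study design gives the timing for the waiting-list arm: "At the 6-month follow-up point, control participants will then be exposed to YES, in a phase 2 exposure".

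Outcome measures lists as a secondary outcome "Emergency care events (ambulance call-outs, accident and emergency attendance or hospitalisations", and closes with a promise that covers every outcome: "For each outcome, we will assess differences in preexposure and postexposure, as well as differences between control and intervention groups".

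Process evaluation adds: "We will also monitor control conditions in the first 6 months to consider whether any extraneous interventions or clinical changes occurred".

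The article does not say whether events will be compared as counts, as proportions with any event, or as rates per unit of time.

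**The concern.** An event count depends on how long one looks. The article fixes look-back periods of different lengths and then promises both before/after and between-arm differences on those outcomes. Two things are at stake.

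First, the randomised contrast. The waiting-list arm is an unexposed comparator only from randomisation to month 6. If the rule assigns no window to that period, the stated windows cannot produce the comparison that randomisation was meant to provide.

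Second, length. Where 12 months are set against 6, an unchanged event rate can look like a fall within phase 2, or like an excess in phase 1 relative to phase 2.

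These data have uses beyond a table of secondary outcomes. Study design says that engagement in diabetes healthcare is one of the effects to be weighed in deciding on a definitive trial, and attendance data bear on it. Health economic evaluation plans to use the records to look at high-cost emergency episodes.

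**Working it through.** **Inputs from the protocol article**
- Pre window, both arms: 12 months before baseline (Data collection and storage).
- Post window: 12 months after exposure for phase 1, 6 months after exposure for phase 2 (same section).
- Control exposure: month 6 (Study design).
- Planned size: "We aim to recruit 50 young people and randomise half to the phase 1 programme exposure, and half to the phase 2 exposure", so 50 / 2 = 25 per arm before drop-out (Participants and sample size).

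**Assumptions**
- Phase 1 exposure falls close to month 0.
- The article gives no event rate. A constant rate λ is assumed, the same in both arms and with no programme effect, over the range 0.1 to 1.0 events per person-year.

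The article states no figure for emergency care that could be reproduced.

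**Step 1: lay out the windows, in months from baseline**

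| Arm | Pre window | Post window | Months in no window |
|---|---|---|---|
| Phase 1 | -12 to 0 (12 months) | about 0 to 12 (12 months) | none |
| Phase 2 (waiting list) | -12 to 0 (12 months) | 6 to 12 (6 months) | 0 to 6 |

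The phase 2 pre window ends 6 months before that arm is exposed. Both post windows contain exposed time only.

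**Step 2: raw counts with no effect**

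Expected events = 25 × λ × (months / 12).
- Phase 2 post/pre = (λ × 6/12) / (λ × 12/12) = 0.50.
- Phase 1 post / phase 2 post = (λ × 12/12) / (λ × 6/12) = 2.0.

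Neither ratio depends on λ or on the number of participants. For example, at λ = 0.3 the 12-month expectation is 25 × 0.3 = 7.5 events and the 6-month expectation is 25 × 0.15 = 3.75.

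**Step 3: any-event proportions with no effect**

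P(at least one event) = 1 − exp(−λ × months / 12).

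| λ per person-year | 12 months | 6 months | Phase 2 post/pre risk ratio | Phase 1/phase 2 risk ratio |
|---|---|---|---|---|
| 0.1 | 9.5% | 4.9% | 0.51 | 1.95 |
| 0.3 | 25.9% | 13.9% | 0.54 | 1.86 |
| 0.5 | 39.3% | 22.1% | 0.56 | 1.78 |
| 1.0 | 63.2% | 39.3% | 0.62 | 1.61 |

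**Step 4: rates per person-time with no effect**

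Phase 2 post/pre = (0.5λ / 0.5 years) / (λ / 1 year) = 1.0, and phase 1/phase 2 is likewise 1.0. Rates therefore remove the length distortion when the underlying rate is constant. They do not restore the randomised contrast, because the two post windows still compare one exposed group with another.

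**The case against.** The strongest reply is that the sentence on windows defines only baseline and post-exposure periods. It does not say that nothing else will be used, and the same paragraph schedules record collection at 6 months with no restriction by arm. Control conditions are also monitored over those months. A reader might infer that the waiting-list arm's month 0 to 6 events will not be collected. The documents do not support that. What stands is narrower: the period has a collection visit but no stated window, and it is the one that the between-arm comparison needs.

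A reader might also infer that the emergency-care comparisons are bound to be wrong. That is not supported either. The ratios of 0.50 and 2.0 arise only with raw counts, proportions are distorted less, and rates remove the length problem. The choice of scale may be settled in an analysis plan that is not shown.

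Nor is the mismatch general. Phase 1 has 12 months on each side, with nearly the same anchor. HbA1c is on the list of record data, but Outcome measures and Data analysis already fix its time points: between arms at 6 months, phase 1 at 6 and 12 months against pre-exposure, and controls at 12 months against their pre-exposure value. That wording separates phase 2 pre-exposure from baseline, so it can be argued that events are meant to be handled in the same way. The rule for events does not say so, however, and the only pre window it gives is the one before baseline.

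Anchoring at exposure is natural for a before/after comparison, and some participants may choose their phase and so have no randomisation date. Both points are fair. Neither supplies a common period for comparing the arms.

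Finally, these are secondary outcomes in a feasibility study that is not powered for effect, and the numeric progression criteria are recruitment and follow-up completion. This limits how serious the point is.

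**Conclusion.** The point holds for record-based event outcomes: emergency care, hospitalisation, and appointment and screening attendance. As stated, the windows give the waiting-list arm no month 0 to 6 period, and that conclusion does not depend on the analysis scale. They also set 12 months against 6, both within phase 2 and between the arms after exposure.

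The size of the length distortion is conditional. With raw counts and a constant rate it is a false halving within phase 2 and a false doubling of phase 1 against phase 2. With any-event proportions, over assumed rates of 0.1 to 1.0 per person-year, the phase 2 post/pre risk ratio is about 0.51 to 0.62 and the phase 1/phase 2 risk ratio about 1.95 to 1.61. With rates per person-time both are 1.0.

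This is worth correcting before data extraction, because a stated rule would be replaced by a better one at little cost. It does not threaten the feasibility aims or the primary clinical outcome.

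**What to change.** Keep the date of every event at extraction and define three windows for every participant in both arms: -12 to 0, 0 to 6 and 6 to 12 months. Count them from randomisation, or from baseline for those who decline randomisation and choose a phase. Then state that:
- the between-group comparison uses months 0 to 6 in both arms, among randomised participants for the randomised contrast;
- the phase 2 before/after comparison sets months 0 to 6 against 6 to 12;
- the phase 1 before/after comparison may stay at -12 to 0 against 0 to 12;
- events are reported as rates per person-month.

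The HbA1c time points need no change.

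The cost is wording in the protocol and on the extraction form, and slightly more extraction and analysis work, since the same records are already being read. The shorter phase 2 pre window will also hold fewer events: at an assumed 0.3 per person-year with 25 participants, 3.75 expected instead of 7.5. The -12 to 0 window can still be reported as a description of baseline.

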In the study outlined in this protocol, we propose to undertake a feasibility trial of the YES programme, with an integrated process evaluation. We have modelled the active ingredients of the programme to target outcomes related to psychosocial well-being, diabetes self-management activation and glycaemic control. In the process evaluation, we will examine methodological, procedural and clinical uncertainties around the YES programme,^30–32^ including: (1) estimates of likely recruitment and retention rates; (2) feasibility and acceptability of data collection instruments and data collection procedures; and (3) feasibility and acceptability of the programme. In line with standard feasibility study objectives,^31^ we will not be testing the effect of the programme on outcomes, although we will estimate the impact of the programme on outcomes, to: consider the feasibility of progression to a definitive trial; and to inform a sample size calculation for such a trial. There will also be a mixed method element to the process evaluation,^32^ to explore: (1) intervention acceptability; (2) the intervention experience and its impact on physical, mental and social well-being; and (3) parents’ perspectives on the programme. These findings will be integrated to formulate potential mechanisms of change following programme exposure.

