**Figure 1 F1:**
[figure not shown]
Consort diagram for the Youth Empowerment Skills programme feasibility study.

We have set the following progression criteria for a subsequent definitive trial: achieve minimum 30% recruitment of eligible participants; and ≥80% completion of final follow-up. We will also assess the impact of the intervention ingredients on target behaviours, including activation of self-management, engagement in diabetes healthcare and improved psychosocial functioning. These effects, alongside impact on glycaemic control, will be used to consider whether there is adequate potency in the programme and will determine whether a definitive trial will be conducted.

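### The 6-month HbA1c effect estimate is fixed as on-treatment on a feasibility rationale that does not support it, although it feeds the go/no-go decision and the definitive-trial sample size

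*Protocol article*

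**What the plan says.** Under Data collection and storage, the protocol article fixes the analysis set and gives its reason: "Analysis will be on-treatment, as the primary aim of this study is to assess feasibility". It does not define on-treatment, and no other section provides for an analysis by randomised arm.

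The Study design and Randomisation sections describe random allocation to immediate YES or a waiting list. Those who decline randomisation may choose their phase. The Data analysis section calls for "the SD of the mean difference between the intervention and control group in HbA1c at 6 months", and Outcome measures adds mean differences between groups over time.

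The results have two stated uses:

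- **Sample size.** Under Participants and sample size: "we aim to estimate the effect-size/SD of outcomes to formulate a power calculation for a definitive trial". The Introduction likewise says "we will estimate the impact of the programme on outcomes", in order to consider progression and to inform that calculation.
- **Go/no-go.** Under Study design, after the figure, on the behavioural and psychosocial effects: "These effects, alongside impact on glycaemic control, will be used to consider whether there is adequate potency in the programme". The same sentence makes this part of deciding whether a definitive trial is run.

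**The concern.** During the first 6 months only the YES arm has sessions to attend. Attendance is therefore a post-randomisation event that, by design, arises in one arm. Selecting or regrouping participants by it sets part of the YES arm, chosen by its own behaviour, against a control arm that has not been selected in the same way. Randomisation no longer protects that contrast.

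The stated reason does not help. A feasibility aim is a good reason to record who attends. It is no reason to condition the effect estimate on attendance, least of all when that estimate is carried into progression and sample size.

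The likely direction can be argued from the article's Introduction, which links disengagement and avoidance with poorer glycaemia. If those who miss the sessions would have done worse anyway, removing them from the YES arm flatters the programme. The potency judgement would then look better, and the planned definitive trial smaller, than the randomised data support.

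**Working it through.** **The plan's own figure.** The total of 50 is consistent with 40 evaluable participants and 20% drop-out: 40/(1 − 0.20) = 50. The base of 40 is back-solved, not stated, but lies within the cited range ("samples of 24–50 are adequate for this purpose"). This total is not in dispute and does not change.

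**Inputs from the article**

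- 25 per arm: half of 50 (Participants and sample size).
- HbA1c threshold of 5.5 mmol/mol (Outcome measures). It defines a clinically significant reduction in a participant, so it serves here only as a yardstick.
- Pilot completion 25/26 (Introduction). Non-completion is 1/26 = 3.8%, rounded to 4%, or one person in 25.

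**Assumptions, not in the article**

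- Non-attendance f in the YES arm runs from 4% to 20%. The upper value borrows the size of the drop-out allowance, which is not itself a non-attendance rate.
- Non-attenders' HbA1c *change* is worse by D = 5 to 10 mmol/mol. Change is used because a gap already present at baseline cancels in change from baseline.
- There is no true effect.

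**Step 1: non-attenders excluded.** Set the mean change to 0 in each randomised arm. Attenders then average −fD and non-attenders (1 − f)D. The spurious benefit is fD.

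**Step 2: non-attenders counted as controls.** The comparison group's mean becomes f(1 − f)D/(1 + f). The spurious benefit is fD + f(1 − f)D/(1 + f) = 2fD/(1 + f).

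| f | D | Excluded, fD | Counted as controls, 2fD/(1 + f) |
|---|---|---|---|
| 4% | 5 | 0.2 | 0.4/1.04 = 0.38 |
| 4% | 10 | 0.4 | 0.8/1.04 = 0.77 |
| 20% | 5 | 1.0 | 2/1.2 = 1.67 |
| 20% | 10 | 2.0 | 4/1.2 = 3.33 |

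All values are in mmol/mol. The largest is 3.33/5.5 = 61% of the threshold; the smallest is 0.2/5.5 = 4%.

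**Step 3: sample size.** If non-attenders gain nothing, the as-randomised effect is (1 − f) times the attender effect. Sample size varies with 1/effect², so the ratio is 1/(1 − f)²:

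- f = 4%: 1/0.96² = 1.09
- f = 20%: 1/0.80² = 1.56

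To put numbers on it, assume also SD 15 mmol/mol, an attender effect of 5.5, two-sided 5% and 80% power. Planning on 5.5 gives 117 per arm.

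- At 20% non-attendance the as-randomised effect is 0.8 × 5.5 = 4.4, which needs 183 per arm. With 117 per arm, power is 61%.
- At the pilot's 1/26 the as-randomised effect is 5.29, which needs 127 per arm. With 117, power is 77%.

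If exclusion also adds the selection shift at f = 20% and D = 10, the on-treatment estimate reads 5.5 + 2.0 = 7.5. Planning then gives 63 per arm, with 38% power for the as-randomised effect of 4.4.

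**The case against.** The strongest reply is that little turns on this in a feasibility study. No effect test is planned, the study is not powered for effect, and the quantities listed under Data analysis are chiefly SDs. With an assumed SD of 15 and 25 per arm, the standard error is 15 × √(2/25) = 4.2 mmol/mol and the 95% half-width about 8.3, which exceeds every shift in the table. The only completion figure for YES is 96%, and at that rate the shift is under 1 mmol/mol.

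Most of this stands, and it limits the size of the point. It does not justify the sentence. Imprecision does not offset a systematic shift, and the article does carry the effect forward, not only the SD. The 96% comes from 26 people who had already taken up a small, non-randomised pilot, so a range is fair.

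Several stronger readings are tempting but unsupported:

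- **That the bias certainly favours YES.** For non-participation in education specifically, the Introduction cites lack of time and a preference for managing alone, not worse HbA1c. All participants already exceed 69 mmol/mol. The direction is plausible, not shown.
- **That non-attenders will definitely leave or switch arms.** The term is undefined, and the sentence follows record windows timed from exposure. The full protocol or SAP may define it.
- **That non-uptake is hidden.** Completion is a stated aim. Education attendance, reach and fidelity are recorded, and decliners are audited.
- **That the definitive trial will be analysed as randomised and so sized for the wrong estimand.** The article does not say so. The Discussion leaves open whether randomisation is feasible and mentions a possible hybrid design.

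**Conclusion.** The point holds in a limited form. The article makes an explicit choice of an on-treatment analysis, supports it with a reason that does not bear on it, and carries the resulting effect into the go/no-go judgement and the next trial's sample size. Either ordinary meaning of on-treatment makes the 6-month contrast depend on attendance after randomisation, so it may be biased, plausibly towards YES.

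The size depends mainly on non-attendance: minor if the pilot's completion recurs, and material against the 5.5 mmol/mol yardstick near 20%. The prognostic gap, the SD and the 20% rate are assumptions. The sample-size ratio matters only if the definitive trial is analysed as randomised, which is usual but not stated. The harm is to an estimate and the decisions built on it, not to type I error.

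The Discussion acknowledges possible bias from the waiting-list design and the preference option, but not from this analysis choice.

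**What to change.** Replace the sentence under Data collection and storage with:

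> The main between-group comparison at 6 months includes all randomised participants with HbA1c data, in the arm to which they were randomised, regardless of attendance; an on-treatment analysis, with on-treatment defined, is supplementary. Participants allocated by preference are reported separately from the randomised comparison.

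Count follow-up completion over all enrolled participants regardless of attendance, and show it separately for randomised and preference participants. A denominator of randomised participants alone would leave out the preference group, to which the 80% progression criterion also appears to apply.

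The cost is a short rewording. HbA1c comes from patient records, so it can be sought whatever the attendance. The total stays at 50 and no new data are needed. The reported effect may look slightly smaller.
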